### Analysis

Analysis will be based on the intention-to-treat principle. Data on GPs lost to follow-up will be extracted from the various databases if possible.

We will analyse covariance using test and drug volumes during the intervention period as the dependent variables, and the baseline data and the explanatory variables as independent variables. The analysis will be repeated using proportions stemming from prescription performance indicators, if available. The unit of allocation to the trial is the LQIC. In larger practices with more than one GP, not all volumes of tests ordered and drugs prescribed will be traceable to an individual GP. In these cases, the unit of analysis will be the practice as a whole. Because of this unit of analysis error, the data will be analysed using multilevel modelling. Data on drugs and tests will be clustered to individual GPs at level one, the practice at level two, the LQIC at level three and the region at level four.

The nature of this study makes it difficult to blind the participants, except for the tests or drugs serving as controls in the other arm. The data analyst will be blinded for the allocation result. Costs of the intervention will be calculated. A cost-effectiveness analysis will be based on these figures. We will use cost minimization analysis from a societal perspective, assuming that the strategy will reduce redundant testing and prescribing. If there are signs of improvement of care (higher scores on the performance indicators), the impact on health may be estimated by modelling the future gains and benefits. Data include costs of coordinating the strategy by the regional contact group, of preparing feedback reports and of chairing the GP groups. The costs of the entire test ordering strategy by [name] were €554.70 per GP per six months (three meetings). The major part of the cost of this strategy consisted of opportunity costs, *viz *the costs of the GPs' time spent attending the session. Because GPs were already attending these meetings and were financially compensated, it seems fair to ignore the opportunity costs. This results in costs of the test ordering strategy of €92.70. The gains obtained by improving test ordering behaviour were €301.00 per GP per six months. Introducing the test ordering strategy would save €208.30 (92.70 to 301.00) per GP per six months [33]. Because prescribing costs are higher, the cost reductions gained by reducing superfluous prescribing should also be higher.

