### Sample size

A sample size calculation is not really possible beforehand, because it is not yet known what working agreements will be created and with respect to what tests or drugs. The specific targets, incorporated in working agreements will probably be based on extreme overuse or underuse of certain tests or drugs by some or all group members. It is possible, for instance, that the group will decide to eliminate a particular obsolete test or drug or create a working agreement to decrease or increase the mean volume of tests ordered or drugs prescribed by 20%, from 35% to 55%.

The sample size calculation used in this trial is as follows: to detect an improvement of 20% in a certain target between groups, assuming an ICC of 0.10 [5], an alpha of 0.05 and a beta of 0.1 and a mean group size of seven, 44 LQICs would be needed. Anticipating a dropout of 10%, we would need to recruit 50 groups. A population this large would account for approximately 900,000 registered patients.

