Fourth, the database on prescriptions consists of data from the large insurance companies in the south of the Netherlands. Using these records as a basis for feedback might create several problems. Although most inhabitants of the southern provinces are insured by one of these companies, prescription data for patients insured with other companies will not be included in our database on prescriptions. This problem might be solved in the future by adding more insurance companies to the database. Another potential problem may be that recording errors are likely to be present in the databases. Desk staff at local pharmacies often links a prescription to one of the GPs in a practice, and often almost all prescriptions for a practice are thus linked to one physician, even when several physicians collaborate in the practice. This creates an inaccuracy in the database, but only for GPs sharing an office. To solve this problem, we will also aggregate to an extra level in these cases, *viz *the subgroup of GPs sharing an office, thus creating a fourth column on the graphical feedback sheet. The last problem we expect to encounter using a large database on prescription is that we do not know the indication for which medication was prescribed; these indications are not known to pharmacists and thus are not stored in any database. This makes it impossible to trace a prescription back to a specific disease. By building a similar database on tests ordered by GPs, we will encounter this problem as well. We do not however expect this to be a problem because we will use graphical comparative feedback. All data from all participating GPs are expected to be equally be affected by this problem and thus the feedback will be comparable.

Fifth, the tests of the diabetes and hypercholesterolemia topics partly overlap. We accepted this, however, because in diabetes, the glucose and HbA1c items are the primary indicators, whereas cholesterol, LDL, HDL, and the ratio are the primary indicators in the hypercholesterolemia topic.

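### The sample size counts seven GPs per LQIC with one ICC, but the analysis treats some practices as single units and adds a practice level, so the stated beta of 0.1 does not describe the planned analysis

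*Protocol article*

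**What the plan says.** **Protocol article, Sample size.** The aim is "to detect an improvement of 20% in a certain target between groups". The example target just before it is a change "by 20%, from 35% to 55" per cent. With one ICC of 0.10 and an alpha of 0.05, the section continues: "a beta of 0.1 and a mean group size of seven, 44 LQICs would be needed". Allowing for 10% dropout, it asks for 50 groups. Neither practices nor regions appear in the calculation.

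**Protocol article, Analysis.** Not all volumes in multi-GP practices can be traced to one GP. The plan then states: "In these cases, the unit of analysis will be the practice as a whole". It turns to multilevel modelling because of this, and sets the hierarchy for all data: "Data on drugs and tests will be clustered to individual GPs at level one, the practice at level two", followed by the LQIC and the region.

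**Protocol article, Discussion (fourth challenge).** For GPs sharing an office, the prescription data are described this way: "often almost all prescriptions for a practice are thus linked to one physician". The remedy given there is an extra column on the feedback sheet, which does not settle the analysis.

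**The concern.** The two sections describe different data. The sizing expects seven separate GP values per LQIC, equally correlated. The analysis expects a mixture: some GP values, some values for a whole practice, and extra correlation within practices. The Discussion indicates that practice-only records will be common for prescriptions, one of the two behaviours the trial targets.

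Multilevel modelling handles correlation among GP records that exist. It cannot supply GP records that do not. A practice with one record has nothing at level one, and the article does not say how such a record enters a model whose first level is the GP.

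At stake is whether the stated power can be relied on, and whether a record pooling several GPs is handled with the right precision.

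**Working it through.** **Inputs from the documents.** 35% vs 55%; ICC 0.10; seven GPs per LQIC; alpha 0.05; beta 0.1; 44 LQICs (50 recruited). Two inferences are needed. First, alpha is two-sided and allocation 1:1, so 22 LQICs per arm. Second, the ICC is at LQIC level, because it is paired with the group size.

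**Step 1: reproduce the plan's figure.** Design effect = 1 + (7 − 1) × 0.10 = 1.6.

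- 90% power: the two-proportion formula gives 128 per arm. 128 × 1.6 / 7 = 29.26, so 30 LQICs per arm, 60 in total.
- 80% power: 96 per arm. 96 × 1.6 / 7 = 21.94, so 22 per arm, 44 in total.

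The printed 44 is matched at 80% power. No variant tried at 90% gives 44: continuity correction gives 64, unpooled variance 58, one-sided testing 48. The match at seven GPs and 1.6 supports the two inferences. The dropout step is consistent: 44 / 0.9 = 48.9, so 49, or 50 for equal arms.

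**Step 2: power on the printed inputs.** With n effective observations per arm, power = Φ[(0.20√n − 1.96 × √0.495) / √0.475], where 0.495 = 2 × 0.45 × 0.55 and 0.475 = 0.35 × 0.65 + 0.55 × 0.45.

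- 44 LQICs: n = 22 × 7 / 1.6 = 96.25; (1.962 − 1.379) / 0.689 = 0.846; power 80.1%.
- 50 LQICs: n = 25 × 7 / 1.6 = 109.4; power 84.9%.

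**Step 3: add a practice level.** Let g be GPs per practice and r the correlation between GPs in one practice, with 0.10 between GPs in different practices of an LQIC. Design effect = 1 + (g − 1)r + (7 − g) × 0.10. The documents give neither g nor r, so both are assumed.

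| g | r | Design effect | Power, 44 LQICs | Power, 50 LQICs | Average ICC implied |
|---|---|---|---|---|---|
| any | 0.10 | 1.6 | 80.1% | 84.9% | 0.100 |
| 2 | 0.3 | 1.8 | 75.3% | 80.5% | 0.133 |
| 3 | 0.3 | 2.0 | 70.7% | 76.2% | 0.167 |
| 2 | 0.5 | 2.0 | 70.7% | 76.2% | 0.167 |
| 3 | 0.5 | 2.4 | 62.7% | 68.3% | 0.233 |

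The last column is (design effect − 1) / 6. The 50-LQIC column assumes that no group drops out.

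**Step 4: does pooling itself cost power?** Take g = 2, r = 0.10. A practice mean has variance (1 + 0.10) / 2 = 0.55. With 3.5 practices per LQIC, the LQIC mean has variance (0.55 + 2.5 × 0.10) / 3.5 = 0.2286. Seven separate GPs give 1.6 / 7 = 0.2286. Properly weighted pooling loses nothing; any loss comes from r above 0.10.

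**Step 5: what weight suits a practice record?** Set total variance to 1 and LQIC variance to 0.10. Within an LQIC a practice record varies by practice variance + GP variance / g. Compare a solo GP with a practice of three:

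- r = 0.1: 0.90 vs 0.90 / 3 = 0.30, ratio 3.0.
- r = 0.3: 0.90 vs 0.20 + 0.70 / 3 = 0.433, ratio 2.1.
- r = 0.5: 0.90 vs 0.40 + 0.50 / 3 = 0.567, ratio 1.6.

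Of these three cases, weighting by GP count (3) is right only at r = 0.1. Treating the record as one GP (1) is right in none.

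**The case against.** **The ICC may already contain practice clustering.** An LQIC-level ICC is normally the average over all GP pairs, including pairs in the same practice. On that reading the design effect stays 1.6 and there is no practice loss. Step 3 instead raises the average ICC to between 0.13 and 0.23. The article does not say which reading applies. This stands, and it is why the 80% figure is the no-loss case and the lower figures are conditional.

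**Baseline adjustment is planned and left out.** This also stands. Dividing the variance by an assumed factor, 1 / (1 − ρ²), with a baseline correlation ρ of 0.5, gives 86% (g = 2, r = 0.3) and 75% (g = 3, r = 0.5) at 44 LQICs; with ρ = 0.3 it gives 79% and 67%. In the no-loss case ρ = 0.5 would reach 90%. The printed calculation has no such term, however, so it cannot be what the stated beta rests on.

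**The plan hedges.** It says a calculation is hardly possible in advance. Its reason is that the working agreements are unknown, not that practices cluster, and it still prints a beta.

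**A stronger reading is tempting.** A reader might count every practice as one yes/no unit with the variance of one GP and infer power as low as 48%. The documents do not support that. Pooling applies only where volumes are untraceable, the outcome is a volume per 1000 patients, and a rate pooled over several GPs is less variable than one GP's. Nor does any text say that a practice record gets a solo GP's weight. The article is silent, and an analysis plan may settle it.

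**Conclusion.** The mismatch stands. The sizing uses seven GP observations and one ICC; the analysis pools some practices, adds a practice level, and still places GPs at level one for all data. The stated beta of 0.1 does not describe that analysis. Nor does it follow from the printed inputs, where 44 LQICs give about 80% power and 50 about 85%.

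How much further power falls cannot be settled from the documents. There is no further loss if 0.10 is the average over all GP pairs. If it holds only between practices, power at 44 LQICs before baseline adjustment is about 75% (two GPs per practice, correlation 0.3) to 63% (three GPs, 0.5). These values rest on assumed practice sizes and correlations, two-sided testing and equal arms. They also use the proportion from the sizing, whereas the main analysis is of volumes. The documents show that the power statement is unsupported; they do not show that the trial is underpowered by a particular amount.

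**What to change.** **Sample size.** Restate the power for 44 and 50 LQICs using 1 + (g − 1) × ICC_practice + (7 − g) × 0.10, over a stated range of g and ICC_practice, with and without baseline adjustment. Say whether 0.10 is the average over all GP pairs or the between-practice value.

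**Analysis.** Enter a practice-only record at practice level, with variance equal to practice variance plus GP variance divided by the number of GPs it pools. Do not enter it as one GP at level one, and do not rely on plain GP-count weights (step 5). Keep GP-level records wherever volumes are traceable. Moving all prescriptions to practice level would discard data needed for inter-physician variation, which is a listed outcome.

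**Cost.** Wording, a recalculation and a slightly more complex model. The number of GPs collaborating in each practice is already collected (Explanatory variables). The stated power becomes less favourable. No extra groups are needed.

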### Objectives

1. To implement the LQIC strategy in the south of the Netherlands, stimulating the relevant parties in the field to take the lead.

2. To determine the critical conditions for effective nationwide implementation.

3. To improve the level of group performance in the participating groups.

4. To reduce undesirable physician variation in test ordering and prescribing; and to reduce underuse or overuse of specific tests and drugs.

5. To examine the costs of large-scale implementation of this strategy, and thus to be able to predict future costs for expansion and maintenance of the strategy.

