#### Effect evaluation

1. The volumes of particular tests ordered and particular drugs prescribed for which the group has agreed that change, either decrease or increase, would be necessary.

2. The total volumes of tests ordered and drugs prescribed by the participating GPs for the clinical topics chosen.

3. The inter-physician variation in test ordering and prescribing behaviour for the clinical topics chosen.

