The existing PTAM group structure in the Netherland is widespread and functions reasonably well. However the need to improve the functioning of these groups is clearly present. Our strategy is known to improve test ordering behaviour of GPs, but is not used widely. Transferring PTAM groups into LQICs gives us the opportunity to add a discussion on test ordering behaviour to existing discussions on prescribing by GPs in PTAMs. The constitution of LQICs therefore is not 'old wine in new bottles' but a completely new approach within existing structures.

Several methodological challenges were encountered when we designed this trial. First, individual GPs are known to choose topics for CME in which they already show good performance [36]. This might result in a 'ceiling effect', meaning that little or no improvement in test ordering or prescribing behaviour would be possible. However, because the LQIC will have to reach consensus on the clinical topics they choose, the risk of such a ceiling effect is probably not very great.

Second, using an implementation strategy on ten different clinical topics from which GPs can choose introduces challenges to the sample size calculation. We chose to leave the LQICs some freedom of choice with regard to the topics. All clinical topics are well-described in the national guidelines for each topic. We will use a set of 204 tests and drugs to generate feedback [See Additional files 2] [See additional file 3]. Because we do not know what agreements local groups will come to, and do not know beforehand what the desired direction for change is, sample size calculation is very difficult. Because we intend to improve care by using the national guidelines, we do not expect to decrease quality of care by this study. However, it is impossible to predict if change will be towards better care.

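### The economic analysis presumes that the strategy removes redundant care and models health effects only if care improves, although the trial also targets underuse

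*Protocol article*

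**What the plan says.** The economic plan stands in a few sentences of the Protocol article, Methods, Analysis. It first announces a cost-effectiveness analysis: "A cost-effectiveness analysis will be based on these figures". The next sentence sets a different method: "We will use cost minimization analysis from a societal perspective, assuming that the strategy will reduce redundant testing and prescribing". Health effects enter on one condition: "If there are signs of improvement of care (higher scores on the performance indicators), the impact on health may be estimated by modelling". No sentence covers falling scores. The same section names performance indicators for prescribing only, and does not promise them: "The analysis will be repeated using proportions stemming from prescription performance indicators, if available".

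Elsewhere the protocol describes a trial in which use may rightly move either way. Objective 4 includes the aim "to reduce underuse or overuse of specific tests and drugs". The first outcome under Effect evaluation is the volume of tests and drugs "for which the group has agreed that change, either decrease or increase, would be necessary". The second methodological challenge in the Discussion says of quality that "we do not expect to decrease quality of care by this study", and then adds: "However, it is impossible to predict if change will be towards better care".

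The cost research question, and the outcome listed under Cost evaluation, are the cost of implementing the strategy and nothing more.

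**The concern.** Cost minimisation ranks options by cost alone. That is legitimate when consequences are known, or convincingly argued, to be the same. Here equality is neither tested nor argued beyond an expectation, and the direction of the result is written into the method as a premise. A cost-effectiveness analysis, the label one sentence earlier, would need an effect measure next to the cost. The two labels have to be reconciled in any case.

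The rule for health effects leans the same way. Better care may earn a modelled benefit, while worse care has no counterpart in the economic analysis. At stake is how the cost result is read. Where the guideline-concordant change is more use, a cost-only comparison shows the strategy as more expensive unless the optional modelling is done. Where volumes fall, the fall is presumed to be redundant care.

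**Working it through.** **Step 1: does the protocol support equal consequences?** The relevant statements, side by side:

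| Place in the Protocol article | What it implies |
|---|---|
| Analysis | Change is taken to be less redundant use |
| Objectives, no. 4 | Underuse is a target as well as overuse |
| Effect evaluation, outcome 1 | Groups may agree on increases or decreases |
| Sample size | The numeric example runs upward, from 35% to 55% |
| Discussion, second challenge | Desired direction not known beforehand; no loss of quality expected; better care cannot be predicted |
| Discussion, fourth challenge | Indications are not recorded for drugs; the same problem is stated for tests |

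Only the expectation of no quality loss favours the premise, and the same paragraph qualifies it. The missing indications mean that volume data alone cannot show whether a reduction was redundant use. The Discussion sets this aside because all GPs are equally affected, so feedback stays comparable. That argument serves comparative feedback; it does not show that a given fall in volume was unnecessary care.

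**Step 2: is the health rule symmetric?** Rising indicators: modelling is allowed, but optional. Falling indicators: nothing is stated. No indicator is named for test ordering, so the documents show no trigger on that side.

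**Step 3: how sensitive is a saving to the premise?** The only cost figures in the document come from the earlier test ordering trial, per GP per six months (Analysis):

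- reduction through changed test ordering: €301.00
- cost of the strategy without GPs' time: €92.70
- stated saving: €208.30

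Reproduction: 301.00 − 92.70 = 208.30, an exact match. The full €301.00 is credited.

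Let f be the share of the reduction that was needed care and is not credited as gain. This share is an assumption; the documents give no value. Then net gain = 301.00 × (1 − f) − 92.70.

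| f | Credited (€) | Net (€) |
|---|---|---|
| 0 | 301.00 | 208.30 |
| 0.10 | 270.90 | 178.20 |
| 0.25 | 225.75 | 133.05 |
| 0.50 | 150.50 | 57.80 |

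Break-even: f = 1 − 92.70/301.00 = 0.692.

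Spending falls by €301.00 whatever f is. What changes is how much of the fall may be described as removed redundant care. Any later cost or health loss from omitted care would come on top.

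**The case against.** Several counter-arguments have weight.

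- **The cost outcome is something else.** A reader might infer that the trial's cost outcome is invalid. The documents do not support that. The research question and the listed outcome are implementation costs, which do not depend on whether changed use was needed. The point concerns the further analysis only. This stands.
- **No booking rule is written down.** A reader might infer that the protocol counts every fall in needed care as a pure saving. It contains no such rule. The cost data it lists are those of coordination, feedback reports and chairing, and €301.00 and €208.30 belong to the earlier trial. The treatment of falls and rises follows from the chosen method, and costing detail may sit in a fuller plan. This stands as a limit on the wording. It does not remove the stated premise, and the Analysis section itself goes on to expect larger savings from prescribing.
- **Worse care would be seen.** A reader might infer that a decline would pass unnoticed. That goes too far: the covariance analysis is to be repeated on prescribing indicators, if available, with no direction fixed. Only the modelling of health impact is one-directional. Corrected underuse may also raise indicators and so open the optional modelling.
- **There is a rationale.** National guidelines are used and no loss of quality is expected, and the premise is openly marked as an assumption. This is fair, but an expectation is not equivalence.
- **The size is assumed.** It is. The protocol fixes no direction for any topic, so no figure can be given for this trial.

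**Conclusion.** The point holds for the further economic analysis described under Analysis. That analysis carries two incompatible labels, rests on an equal-consequences premise that the objectives, the first effect outcome and the Discussion undercut, and admits health effects only when they favour the strategy. Its conclusion is therefore one-sided as written. Implementation cost and the effect evaluation are unaffected.

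The size for this trial cannot be derived. On the earlier trial's figures, the gain attributable to redundant care would fall from €208.30 to €133.05 at an assumed 25% of needed care and reach zero at about 69%. This shows sensitivity to the premise and is not an estimate. The conclusion rests on reading cost minimisation in its usual sense and on the article's text; a fuller plan could already settle the costing rules.

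**What to change.** 1. Delete the assumption that the strategy will reduce redundant testing and prescribing, and use one name for the analysis.
2. Replace cost minimisation with a cost-consequence presentation: implementation cost per GP; change in test costs and drug costs by topic, in either direction; and, beside these, change in prescribing indicators where available.
3. Split the cost changes by the agreed direction of change. Under Measurements, each group's targets are recorded after every session, so this needs no new data. Groups in the other arm set no targets on that topic, so the split is descriptive; show their change on the same items next to it.
4. Make the modelling trigger symmetric: consider health impact when indicators rise and when they fall.
5. Describe lower volumes as a cost reduction, and as removed redundant care only where the indicators support it.

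A rule that credits savings only for obsolete items would not work from the documents. Clinical topics says that the sets contain both accepted and obsolete items, but not that each item is classed.

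The cost is mainly rewording and one reporting table; Clinical topics already foresees indicative prices for each test and drug. The downside is that topics with mixed direction yield no single net-saving figure. Objective 5 asks for implementation costs and a prediction of future costs, and needs no such figure.

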Grol has identified in his model of effective implementation six stages in quality of care improvement[25]. In the first stage, new research findings, new guidelines, experienced weaknesses, or best practices create an opportunity for quality improvement. In the second stage, after the initial implementation process has been planned, targets for improvement or change are set. Prior to the actual implementation, the performance, target group, and setting are analysed. In the fourth stage, the strategies that are to be used are identified and tested. The implementation is developed, tested, and executed. Finally, the implementation is evaluated and adapted, if necessary [25]. The present study will deal with the actual sustainable transfer of a successful implementation strategy to the field. We are not aware of published studies testing this process, or whether effects are sustainable when transferred to the field. Nor are we aware of published studies on the implementation of a large-scale strategy aimed at influencing both the test ordering and prescribing behaviour of GPs simultaneously, using peer review and social influencing in primary care collaboratives.

In the Netherlands, existing networks of pharmacotherapeutic audit meetings (PTAM) can be used to disseminate and implement guidelines on test ordering and prescribing. The goal of setting up these meetings by primary care providers was to improve the quality of their prescribing behaviour [26]. The local groups usually consist of six to ten GPs with affiliated community pharmacists [27]. During the meetings, they discuss the choice of drugs in the context of a specific illness or disease. In recent decades, this form of CME has gained widespread acceptance amongst GPs and policymakers in the Netherlands. However, these sessions tend to offer little or no room for discussions on test ordering. Because no other system of regular meetings exists, the possible underuse, overuse, and misuse of diagnostic services is not discussed by primary care providers on a regular basis.

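### The cost analysis is labelled societal but argues for ignoring GPs' attendance time, and in the figures the plan relies on that choice decides whether the strategy saves or costs money

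*Protocol article*

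**What the plan says.** The Analysis section of the protocol article fixes type and perspective in one sentence: "We will use cost minimization analysis from a societal perspective, assuming that the strategy will reduce redundant testing and prescribing". The sentence before it announces a cost-effectiveness analysis. The cost items named for this trial are these: "Data include costs of coordinating the strategy by the regional contact group, of preparing feedback reports and of chairing the GP groups". GPs' attendance time is not among them.

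The section then turns to the earlier trial of the test-ordering strategy. Its costs "were €554.70 per GP per six months (three meetings"), and the larger part of that sum was "the costs of the GPs' time spent attending the session". The argument for setting this part aside is: "Because GPs were already attending these meetings and were financially compensated, it seems fair to ignore the opportunity costs". The article continues: "This results in costs of the test ordering strategy of €92.70". Against this it sets the benefit: "The gains obtained by improving test ordering behaviour were €301.00 per GP per six months". It concludes that the strategy would save €208.30 per GP per six months and expects prescribing to bring larger reductions.

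On the existing pharmacotherapeutic meetings, the Background says: "However, these sessions tend to offer little or no room for discussions on test ordering". The Intervention section gives test ordering its own session of about 90 minutes for each topic. The Discussion describes test ordering as something added to the existing talk about prescribing.

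**The concern.** A societal perspective values resources by what they could otherwise have been used for, whoever pays. GPs' time in a meeting is such a resource. Paying them for it shifts the burden to the payer but does not make the time free.

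That GPs already attended is a better argument, but it supports a zero incremental cost only if the strategy neither adds meeting time nor pushes out discussion of value. The article does not show this. It says test ordering had hardly any place in the existing meetings and now receives sessions of its own. That time must be either new or taken from something else.

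The cost of implementation is one of the three research questions in the Abstract, and Objective 5 is to predict the cost of expanding and maintaining the strategy. A result called societal that leaves out its largest component could mislead that decision.

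A smaller issue is the type of analysis. Cost minimisation presupposes equivalent outcomes, and the article adds an assumed reduction in volumes. Yet Objective 4 covers underuse as well as overuse, and the first effect outcome allows agreed increases.

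**Working it through.** **Inputs** (Protocol article, Analysis; all per GP per six months, all from the earlier test-ordering strategy):

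- Full cost, three meetings: €554.70
- Cost with opportunity costs ignored: €92.70
- Gain from changed test ordering: €301.00
- Saving stated in the article: €208.30

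**1. Reproduce the stated saving.** Gain minus cost without GP time: 301.00 - 92.70 = **€208.30**, an exact match.

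**2. GP time implied by the two cost totals.** 554.70 - 92.70 = **€462.00**. As a share of full cost: 462.00 / 554.70 = 83.3%. Per meeting: 462.00 / 3 = €154.00.

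**3. Net result with all GP time counted.** 301.00 - 554.70 = **-€253.70**.

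**4. Net result by share counted.** The article does not say how much of the time is additional or displaced, so the share s is an assumption and is shown over its whole range. Net(s) = 208.30 - s × 462.00.

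| Share of GP time counted | Net per GP per six months |
|---|---|
| 0% | +€208.30 |
| 25% | +€92.80 |
| 50% | -€22.70 |
| 75% | -€138.20 |
| 100% | -€253.70 |

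**5. Break-even share.** Setting Net(s) = 0 gives s = 208.30 / 462.00 = **45.1%**.

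Within these figures, the sign therefore depends on one quantity, and the article's reasoning sets that quantity to zero without evidence from the meetings themselves.

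**The case against.** The strongest reply is that the euro figures describe another trial. They are in the past tense, cover tests only, and rest on three meetings. This trial has two sessions per topic for three topics, and the article expects larger savings from prescribing. The remark about opportunity costs stands within that discussion, and no sentence says outright that GP time will be left out of this trial's costing. Much of this stands: neither +€208.30 nor -€253.70 predicts this trial's result. What remains is that the article uses these figures as its economic case, argues for the exclusion in general terms, and names no attendance time among this trial's cost items.

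A second reply is that the groups are stable, already meet, and are already rewarded for attending. If trial sessions occupy regular slots, little or no incremental time is a recognised costing position. This also stands in part. A reader might infer from the Background that the test-ordering sessions are extra hours, but that passage concerns the content of meetings, not their number or length. The article gives no count of meetings before or during the trial. The additional share is unknown, and displaced discussion could still have value.

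A reader might also infer that training, moderator and pharmacist time are left out because they are not listed. The list is introduced as what the data include, not as complete, and a condensed article commonly leaves itemised costing to the full protocol. The point does not rest on this.

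Nor would it be fair to say that the article commits to cost minimisation alone. It also names cost-effectiveness and allows health effects to be modelled if performance indicators improve. What stands is that the two labels conflict and that a reduction is assumed.

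Finally, the exclusion is open and argued, and both cost totals are printed. That makes it easy to correct but does not make it consistent with the stated perspective.

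**Conclusion.** The concern holds as a conflict between the stated perspective and the proposed handling of the largest cost item. In the figures the article relies on, GP time is €462.00 of €554.70, and the share counted moves the net from +€208.30 through zero at about 45% to -€253.70.

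This rests on two conditions. The figures are those of the earlier test-ordering strategy, without prescribing savings. The value of -€253.70 is the bound with all GP time counted as additional or displaced. The documents do not support the stronger reading that the strategy, or this trial, makes a loss of that size: the true share is not given, and prescribing could alter the result in an amount the article does not quantify.

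The randomisation and the effect analyses are untouched. The cost conclusion is affected, because its sign can change.

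**What to change.** 1. In the societal base case, count GPs' attendance time to the extent that it is additional to, or displaces, existing meeting time.
2. Report the result without GP time as a labelled sensitivity analysis, together with the break-even share.
3. If GP time is to stay out of the main result, rename the perspective incremental implementation cost and do not present the saving as societal.
4. Reconcile the cost-minimisation and cost-effectiveness labels. Report net costs beside the effects on volumes and performance indicators, without assuming a reduction, so that corrected underuse can appear as higher volume.

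**Cost.** The reported saving becomes less favourable. Attendance is already recorded, and the chair already completes a form after each meeting. The listed content of that form covers neither how long the session lasted nor whether it replaced a regular meeting, so an item on both should be added. Without it, the break-even share cannot be compared with what happened.
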